### Outcomes

The primary outcome is the overall average compliance to the selected active ERAS elements (Table 2). Since the application is patient-centred and focusses on empowering patients to get in control of their own health, the PROMs, such as health related quality of life and patient satisfaction, are considered important secondary outcome parameters. Other secondary outcomes include postoperative outcome parameters (e.g. complications), gastro-intestinal recovery (e.g. time to passage of stool), activity and pain measurements. Table 5 describes all study outcomes and how and when these will be measured.

**Table 5 Tab5:** Time points and measurements

Enrolment		T0	T1	T2	T3	T4	T5	T6	T7	Registered in/with:
	Eligibility screen	x								
	Informed consent	x								
	Allocation	x								
Interventions		T0	T1	T2	T3	T4	T5	T6	T7	
Intervention group	Download mobile application	x								
	Wear activity tracker		O	O	O	O	O	O		
Control group	Wear activity tracker		O	O	O	O	O	O		
Data measurements		T0	T1	T2	T3	T4	T5	T6	T7	
Baseline characteristics	General characteristics	x								Sex, age, ASA, BMI, smoking, alcohol intake
	Disease related characteristics	x								Disease, operation
	eHealth literacy assessment	x								eHEALS
Protocol compliance *(as reported by patients)*	1. Cessation of smoking and excessive intake of alcohol	x								Y/N questions in app or with paper form
	2. Preoperative nutritional screening and, as needed, assessment and nutritional support	x								Y/N questions in app or with paper form
	3. Preoperative carbohydrate treatment			x						Y/N questions in app or with paper form
	4. Preoperative prophylaxis against thrombosis			x						Y/N questions in app or with paper form
	5. Early mobilization (day of surgery)				O	O				Y/N questions in app or with paper form
	6. Early intake of oral fluids and solids (offered the day of surgery)				O	O				Y/N questions in app or with paper form
	7. Early removal of urinary catheters and intravenous fluids (morning after surgery)					O				Y/N questions in app or with paper form
	8. Use of laxatives					O				Y/N questions in app or with paper form
	9. Intake of protein and energy-rich nutritional supplements					O				Y/N questions in app or with paper form
	10. Prepare for early discharge					O				Y/N questions in app or with paper form
Postoperative data ≤30 days *(retrospective collection)*	Length of hospital stay								x	EHR
	Overall morbidity ≤30 days								x	EHR
	Complications								x	Clavien-Dindo minor: I-II major: III-V
	Reoperations								x	EHR
	Readmission ≤30 days								x	EHR
	In-hospital mortality								x	EHR
Gastrointestinal	Tolerance of solid food				O					Days
	Absence of nausea				O					Days
	Passage of first flatus				O					Days
	Passage of first stool				O					Days
	Weight - preoperative			x						Weight at admission, KG
	Weight - at discharge				x					Weight at discharge, KG
Activity	Mean preoperative physical activity (steps/day)		O							Activity tracker, steps per day
	Postoperative physical activity (steps/day)				O	O	O			Steps per day
Pain	Perceived pain daily postoperative - discharge				O					NRS 1–10*
	Compliance with intake of (pain) medication				O					Y/N questions in app or with paper form
Self-registered questionnaires		T0	T1	T2	T3	T4	T5	T6	T7	
PROMS	General quality of life (WHOQol)	x				x	x		x	WHOQoL - BREF
	Multidimensional fatigue assessment	x						x	x	Multidimensional fatigue inventory
	Physical Activity (IPAQ)	x				x		x	x	IPAQ-short
	Disability	x							x	WHODAS2
	Patient satisfaction questionnaire								x	Self-developed patient satisfaction questionnaire

T0: Moment of randomization; T1: 1–7 days before stay in hospital; T2 hospital admission; T3: day of surgery; T4: 1–7 days after surgery; T5: 8–14 days after surgery; T6: 15 days – 21 days after surgery; T7: 22–42 days after surgery

x: the event/action is performed or assessed once in the indicated time slot. O: the event/action is performed or assessed continuously in the indicated time slot. *Numeric rating scale

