### Control and intervention group

#### APPtimize study group

Patients in the intervention group will receive instructions how to download the APPtimize application shortly after the operation is scheduled. The application will be used until 42 days postoperative. The selected ERAS elements (Table 2) have been translated into practical patient-tailored features that can be viewed in the application any time but will also be brought to the patient’s attention through push notifications (Table 3) at set times. The push notifications attempt to prompt the patient to undertake action towards an ERAS element that requires action at that specific moment. The main goals of the application are: to inform and educate the patient, to stimulate patient participation throughout the perioperative care pathway, and to monitor daily activity. All information provided by the application can be accessed at any moment but also once an ERAS element of the care pathway is considered completed. Figure 1 illustrates the layout of the application, with the third screenshot showing the application’s feature ‘dashboard’. This feature represents the completion of three subjects: 1. completion of the daily set activity goal 2. completion of the active ERAS elements, and 3. completion of self-registered questionnaires throughout the entire study.

**Table 3 Tab3:** Push notifications

Preoperative day	Notification
−21	Information about nutrition
−20	Information about smoking
−16	Information about preparation before surgery
−8	Instructions to wear the activity tracker
−2	No alcohol 24 h before surgery
−1	Instructions to drink the pre-operative nutrition drink (4x)
0	Instructions to drink the pre-operative nutrition drink (1x)
Postoperative day	Notification
0	Instructions to wear the activity tracker
1,2,3,..,day of discharge	information of daily goals
1,2,3,..,day of discharge	Information on progress of daily activity
1,2,3,..,day of discharge	Check progress to discharge in the overview of ‘completion of goals’

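### Table 5 records smoking and alcohol cessation, a primary-outcome element, only at randomisation, so as scheduled it cannot show an effect of the app

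*Protocol article*

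**What the plan says.** The Outcomes section defines the endpoint: "The primary outcome is the overall average compliance to the selected active ERAS elements (Table 2"). It then makes Table 5 the governing schedule: "Table 5 describes all study outcomes and how and when these will be measured".

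In Table 5 two of the ten elements have one mark each, in column T0:

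- "1. Cessation of smoking and excessive intake of alcohol"
- "2. Preoperative nutritional screening and, as needed, assessment and nutritional support"

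The legend gives "T0: Moment of randomization" and says that an x means assessed once in that slot. Allocation and the app download are also marked at T0. So are smoking and alcohol intake, as baseline characteristics.

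Table 3 (APPtimize study group) sends nutrition information on day −21, smoking information on day −20 and "No alcohol 24 h before surgery" on day −2.

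Among the secondary outcomes, tolerance of solid food, absence of nausea, first flatus, first stool, pain, medication intake and weight at discharge are marked in one column only, "T3: day of surgery". The pain row is nevertheless labelled "Perceived pain daily postoperative - discharge". Postoperative steps are marked T3 to T5, while the rows for wearing the tracker run to T6.

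**The concern.** A compliance element can contribute to a comparison of arms only if it is observed after the intervention has had a chance to act. Cessation of smoking and excessive drinking, asked once at randomisation, describes the patient on entry. Randomisation balances that status between arms on average, so the element adds noise and, in expectation, no difference. It carries one tenth of the primary score.

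Table 5 drives the questions in the app and on the paper form. If it is implemented as printed, change in smoking or drinking between randomisation and surgery is not captured under any scheduled item, and it would be hard to recover reliably afterwards.

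Element 2 shares the timing problem but not the clear direction. Content development says that both sites practise almost all elements as usual care, with nutritional screening one of the exceptions, and that the team chose to put it in the app. The arms could therefore differ on it, depending on what the T0 answer is taken to cover.

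**Working it through.** **Timing, side by side**

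| Item | Recorded (Table 5) | Earliest app action |
|---|---|---|
| Element 1, smoking and alcohol | T0, once | Download at T0; prompts on days −20 and −2 |
| Element 2, nutrition | T0, once | Download at T0; prompt on day −21 |
| Smoking and alcohol intake, baseline | T0, once | not applicable |

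Element 1 and the baseline smoking and alcohol items share a time point, and both prompts come after it. A fault in table extraction is unlikely: the rows have consistent field counts, and neighbouring rows fall in sensible columns (carbohydrate treatment and preoperative weight at T2, 30-day data at T7).

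**The plan's own sample size**

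Inputs from Sample size calculation: 57% against 62%, so a difference of 5 points; SD 9; two-sided alpha 0.05; power 90%; 70 per group; 10% loss.

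- Two-sample t-test: 69.06 per group, rounded up to 70. This reproduces.
- Total: 2 × 70 / 0.9 = 155.6, rounded up to 156. This reproduces.
- Power at 70 per group: noncentrality = 5 / (9 × √(2/70)) = 5 / 1.521 = 3.29, giving 90.4%.

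**Illustration of dilution**

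Assumptions, none of them in the protocol: inert elements differ by 0 points, every other element differs by 5 points, the ten elements have equal weight, and the SD of the average stays at 9.

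- Element 1 inert: 9 × 5 / 10 = 4.5 points. Noncentrality 4.5 / 1.521 = 2.96; power 83.6%.
- Elements 1 and 2 inert: 8 × 5 / 10 = 4.0 points. Noncentrality 4.0 / 1.521 = 2.63; power 74%.
- To reach 5 points overall, the responsive elements would need 5 × 10 / 9 = 5.56 points (one inert) or 5 × 10 / 8 = 6.25 points (two inert).

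Sensitivity to the SD, at 70 per group:

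| Overall difference | SD 7.2 | SD 9 | SD 10 |
|---|---|---|---|
| 4.5 points | 96% | 84% | 75% |
| 4.0 points | 90% | 74% | 65% |

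**Secondary-outcome marks**

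- Solid food, nausea, flatus and stool: marked T3 only, but the recording unit is days.
- Pain: marked T3 only, but the label runs to discharge.
- Medication intake: marked T3 only, beside the pain row.
- Weight at discharge: marked T3 only, yet Study population excludes patients with an expected stay of 3 days or less, so discharge is not expected on the day of surgery.
- Postoperative steps: end at T5 (day 14), but Activity tracker, APPtimize study group and Control group all have the tracker worn to day 21, which falls in T6.

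**The case against.** **T0 may be loosely labelled.** Intervention patients can answer in the app only after downloading it, so their answers cannot strictly precede download. T1 starts seven days before admission, so the table has no column for the weeks that hold the earlier prompts, and T0 may be standing in for the whole preadmission phase. This is plausible, but it is an inference. The legend calls T0 the moment of randomisation, and an x means a single assessment. If the broader meaning was intended, the legend needs correcting, so the passages must be reconciled either way.

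**The control diary may cover it.** Control patients complete a daily checklist of ERAS elements. The Control group section gives no start date, and Table 5 gives elements 1 and 2 no later slot, so the diary does not displace the schedule.

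**The day −2 prompt is not element 1.** It concerns alcohol in the last 24 hours, which differs from stopping excessive intake. That is fair, but the smoking prompt on day −20 also follows T0, and the argument does not depend on the alcohol prompt.

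**A fifth of the primary score is lost and power is 74%.** A reader might infer this from the two T0 marks. The document does not support it as a finding. For element 2, the app offers something that usual care omits, so neither a zero difference nor a pull towards the null is established. The protocol also states its 5 points for the overall average and expects larger gains on some elements, so assigning 5 points to the responsive elements alone is a chosen scenario.

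**Bowel recovery, pain and discharge weight cannot be observed.** A reader might infer this from the T3-only marks. The row labels, the recording units and the tracker text largely show the intended timing. These are errors in the marks and do not touch the primary outcome.

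**Conclusion.** The point stands for element 1. As printed, Table 5 measures it at a time when only baseline status can be seen, duplicates baseline items already collected, and conflicts with later prompts in Table 3. Element 2 has the same timing defect, but the direction of its effect on the comparison is uncertain.

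The consequence is avoidable dilution of the primary score. Its size is not fixed by the protocol: about 84% power if element 1 alone is inert and about 74% if both are, resting on the assumed 5-point gain elsewhere, equal weights and an unchanged SD of 9. The planned sample size itself reproduces and is not in question here.

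The secondary-outcome marks are real contradictions but minor.

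**What to change.** 1. In Table 5, record element 1 at T2 (hospital admission) in both arms, with the question worded to cover the period from randomisation to admission. Do the same for element 2. T2 is not the only possible choice, but it already exists and falls after most of the preoperative prompts.
2. Keep smoking and alcohol status at T0 as baseline characteristics only, and do not count them in the compliance score.
3. If T0 was meant to span the preadmission phase, correct the legend so that it agrees with Table 3 and with the meaning of x.
4. Extend the marks for bowel recovery, pain, medication intake and discharge weight from T3 through discharge, and add T6 to postoperative steps.

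The cost is an edit to Table 5, the app's question schedule and the paper form, with no extra visit. The article states that data collection had not begun at submission, so the change could be made before any affected data were recorded.

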### Investigational intervention

#### Content development

A consensus meeting was organized with a multidisciplinary team of caregivers, representing both Amsterdam UMCs’ locations. Both locations practice almost all the elements from the 2012 ERAS society recommendations for colorectal surgery as part of their ‘care as usual’ except for ‘nutritional screening’ and ‘chewing gum as a laxative’. [9] Active ERAS elements, elements that depend on patient involvement, were included in the application. The multidisciplinary team of caregivers evaluated the ERAS elements for their eligibility to be included in the application. Although ‘nutritional screening’ was not part of current ‘care as usual’, the multidisciplinary team thought it would be useful to include this element in the application. Table 2 displays all elements that were included in the application. In ‘Additional file 1’, one can find the functional design of the application. The functional design illustrates the workflow through the application and the basic layout. After the first version of the application will be developed, ‘patient experts’ will be invited to test the application and review the content of the application.

**Table 2 Tab2:** ERAS elements in the APPtimize application

Preadmission	
1. Cessation of smoking and excessive intake of alcohol	
2. Preoperative nutritional screening and, as needed, assessment and nutritional support	
Preoperative	
3. Preoperative carbohydrate treatment	
4. Preoperative prophylaxis against thrombosis	
Postoperative	
5. Early mobilization (day of surgery)	
6. Early intake of oral fluids and solids (offered the day of surgery)	
7. Early removal of urinary catheters and intravenous fluids (morning after surgery)	
8. Use of laxatives	
9. Intake of protein and energy-rich nutritional supplements	
10. Prepare for early discharge	

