### Data analyses

Statistical analyses of any difference between the two study groups will be performed using SPSS for Windows version 25 or higher (SPSS Inc. Chicago, IL). Data will be analysed according to intention to treat protocol. If applicable, missing data will be imputed. Baseline characteristics will be summarized using descriptive statistics and compared between the intervention and control groups. Continuous data will be reported as mean and standard deviation in case of normal distribution and as median 95% confidence intervals in case of non-normal distribution. Normality of the data distribution will be analysed by visually inspecting the histograms and Kolmogorov-Smirnov test. Comparative analysis will be done using a two-sided t-test in case of normal distribution and by means of the Mann-Whitney U test in case of non-normal distribution. *P*-values of ≤0.05 will be considered statistically significant.

Categorical data will be displayed as numbers and percentages and analysed using a Chi-square test.

Investigational site, surgical procedure, age, and score on the eHealth literacy test will be taken into account as covariates in the adjusted analyses. Intended subgroup analyses will be conducted for the surgical procedure.

To estimate the primary outcome, the overall average compliance to the selected active ERAS elements, the elements will be scored as ‘completed’ or ‘not completed’ (dichotomous), as described by the ERAS protocol. For example, the urine catheter should be removed on day one after surgery. If this could not take place, the element was scored as ‘not completed’. For both the intervention and control groups, the proportion of completion of each individual active element will be calculated. The overall compliance is an average of the individual completion percentages. The protocol compliance is a continuous variable and will be reported as mean and standard deviation in case of normal distribution and as median and 95% confidence intervals in case of non-normal distribution.

The relation of the use of the application with the secondary outcomes mentioned in Table 5 will be examined with a linear regression.

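### Two of the ten equally weighted primary compliance elements (smoking/excessive alcohol, and nutritional screening) are scheduled once, at randomisation, and so reflect essentially pre-intervention status

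*Protocol article*

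**What the plan says.** All references are to the Methods of the protocol article.

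- **Primary outcome.** The Outcomes section makes it the overall average compliance to the elements of Table 2, a list that runs to "10. Prepare for early discharge". Data analyses adds: "The overall compliance is an average of the individual completion percentages". Each element therefore counts one tenth.
- **Timing.** The Outcomes section presents Table 5 as the statement of how and when every outcome is measured. "1. Cessation of smoking and excessive intake of alcohol" and "2. Preoperative nutritional screening and, as needed, assessment and nutritional support" have one mark each, at T0, and none at T1 or T2. The note reads "T0: Moment of randomization" and explains that an x means a single assessment in that slot. Elements 3 and 4 are marked at T2 (hospital admission), and elements 5 to 10 at T3 and/or T4.
- **Baseline.** The general characteristics, also taken at T0, are "Sex, age, ASA, BMI, smoking, alcohol intake".
- **Intervention.** Table 5 places the app download at T0. Table 3 sets the nutrition prompt for preoperative day -21 and "Information about smoking" for day -20.
- **Other recording.** The Control group section gives controls a once-daily diary checklist of ERAS elements. The APPtimize study group section describes an app dashboard that shows completion of the active elements. Neither states when elements 1 and 2 are scored.

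**The concern.** An outcome component has to be measured after the intervention has had a chance to act. Here two components are scored at the point of allocation, when the app is only being installed. For element 1, the answer largely repeats the smoking and alcohol status collected at the same time as a baseline characteristic. For element 2, the timing is especially unfortunate: Content development says that nutritional screening was not part of usual care at the two locations and was deliberately put in the app, so there should be room for the arms to differ.

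Two things are at stake. First, components with an expected app effect near zero pull the average difference towards zero. Second, a difference that did appear at T0 would be hard to read. Participants are not blinded, and answers are given in the app in one arm and on paper in the other. Such a difference would more likely reflect reporting or recording than use of the app.

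**Working it through.** **1. Order of events**

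| Event | Timing | Source |
|---|---|---|
| Allocation, app download, baseline smoking and alcohol | T0 | Table 5 |
| Elements 1 and 2 scored (once) | T0 | Table 5 |
| Nutrition prompt | Day -21 | Table 3 |
| Smoking prompt | Day -20 | Table 3 |
| Elements 3 and 4 scored | T2, admission | Table 5 |
| Elements 5 to 10 scored | T3 and/or T4 | Table 5 |

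No app content can reach a patient before download. The article allows for surgery scheduled less than 7 days ahead, and for such patients the handling of the day -21 and -20 prompts is not stated. Even then, exposure cannot precede T0.

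**2. Weight in the primary score**

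2 / 10 = 20%.

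**3. The plan's own sample size**

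Inputs from Sample size calculation: difference 62 - 57 = 5 points, SD 9, two-sided alpha 0.05, power 90%, loss to follow-up 10%.

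- Normal approximation: n = 2 × (1.960 + 1.282)² × 9² / 5² = 68.1, so 69 per arm.
- t-test solution: 69.06, so 70 per arm.
- Total: 140 / 0.9 = 155.6, so 156.

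The stated 70 and 156 are reproduced. Power at 70 per arm is 90.4% (t-test).

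**4. Effect of two inert elements**

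Overall difference = (sum of the ten element differences) / 10, with elements 1 and 2 set to 0.

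- To reach +5 overall, the other eight must average 5 × 10 / 8 = 6.25 points.
- If the other eight gain 5 points each, the overall difference is 8 × 5 / 10 = 4.0 points.

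**5. Power at a 4.0-point difference, 70 per arm, two-sided 0.05**

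Standard error of the difference = SD × √(2/70). At SD 9 this is 1.521, and 4 / 1.521 = 2.629. Normal-approximation power is Φ(2.629 - 1.960) = 0.748.

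| SD | Normal approximation | t-test |
|---|---|---|
| 7.2 (SD shrinks in proportion, 0.8 × 9) | 90.8% | 90.4% |
| 8 | 84.1% | 83.6% |
| 9 (plan) | 74.8% | 74.3% |
| 10 | 65.8% | 65.2% |

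The article gives only SD 9; the other values are assumptions that show the range.

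**The case against.** **Table 5 may be loose rather than deliberate.** It has no column between T0 and T1 (1 to 7 days before the hospital stay), so T0 may stand in for the whole preadmission period under which Table 2 files both elements. Other marks are plainly approximate: discharge weight and first stool appear only at T3, the day of surgery. This has force, and the T0 mark may be a slip. But no section gives another time, and the timing of a primary outcome component has to be right either way.

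**Exposure starts at download.** App content can be viewed at any time, and a patient who answers in the app has already installed it. The order of download and answer within T0 is not stated. A reader might infer that these elements cannot respond to the app at all, or that an effect on them could never be seen. The article does not support anything so absolute, particularly for element 2, which could differ at once if the app delivered screening on installation. What stands is that a single answer at T0 reflects essentially pre-intervention status.

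**The diary and the dashboard may capture these elements later.** Neither text excludes them, but neither gives them a time. The diary is for controls only. If it were used to score them later while app users were scored at T0, the arms would be measured at different times.

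**The alcohol message.** Table 3 also has an alcohol prompt on day -2. It concerns abstinence in the 24 hours before surgery, which is not clearly the same as stopping excessive intake, so the point does not rest on it.

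**The power loss is hypothetical.** This is correct. The article plans +5 on the overall average and expects some elements to gain more. An average gain of 6.25 on eight elements is compatible with that.

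**Conclusion.** The point holds as a defect in the timing of the primary outcome. As scheduled, 20% of the primary score is collected essentially before the intervention, and nothing elsewhere in the article supplies a later assessment. The result is a diluted contrast and two components in which any difference between arms is more plausibly a reporting artefact than an app effect. This conclusion rests on Table 5 being followed as written and on equal weighting of the ten elements. It does not depend on any power figure.

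A reader might go further and infer that the trial is underpowered at 74%. The article does not support that as a finding: 156 is correct for a true 5-point overall difference. The 74% requires two added assumptions, namely that the other eight elements gain exactly 5 points each and that the SD stays at 9. Under the same gain, power runs from about 65% at SD 10 to about 84% at SD 8, and stays near 90% if the SD shrinks to 7.2. The firm arithmetic consequence is narrower: if the two elements are inert, the remaining eight must average +6.25 points to deliver the planned difference.

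**What to change.** - In Table 5, move the outcome mark for elements 1 and 2 from T0 to T2 (hospital admission), alongside elements 3 and 4.
- Use the same yes/no wording in both arms, with an explicit reference period from randomisation to admission.
- Keep the T0 answers as baseline values only, outside the compliance score.
- Reconcile Table 5 with Tables 2 and 3, the control diary and the app dashboard, so that one stated time applies to these two elements in both arms. If the T0 mark was a slip for a later assessment, correct it in the same way.

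The cost is one table correction and two questions on a form or app screen already completed at admission. It needs no extra visit and no extra patients, and the sample size calculation does not have to change. The abstract states that data collection had not begun at submission, so the change could be made before enrolment.
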